### 11.7.1. Analysis of the Primary Outcome Measure

The primary outcome will be the diagnostic performance of intraoperative CLI + FAR LightPath® imaging, assessed using a confusion matrix to describe the relationship between the results of tumour margin assessment (positive or negative) with CLI + FAR LightPath® imaging and standard-of-care histopathology (positive or negative) (gold standard).

| Standard-of-care histopathology |          |       |
|---------------------------------|----------|-------|
| Positive                        | Negative | Total |

|                                    |          |        |        |     |
|------------------------------------|----------|--------|--------|-----|
| CLI + FAR
LightPath®
imaging | Positive | a (TP) | b (FN) | a+b |
|                                    | Negative | c (FP) | d (TN) | c+d |
|                                    | Total    | a+c    | b+d    | n   |

Sensitivity =  $a/(a+c)$

Specificity =  $d/(b+d)$

Overall agreement =  $(a+d)/(a+b+c+d)$

TP = true positive; FP = false positive; FN = false negative; TN = true negative

The primary outcome measures are sensitivity, specificity and overall accuracy.

The following diagnostic accuracy statistics will be presented (as a percentage together with 95% exact confidence intervals):

- Sensitivity - The proportion of subjects with positive margin confirmed by histopathology who have a positive result on LightPath® Imaging.
- Specificity - The proportion of subjects with clear margin confirmed by histopathology who have negative result on LightPath® Imaging.
- Overall accuracy - The proportion of subjects whose margin status is correctly classified by LightPath® Imaging
- Positive predictive value - The probability of positive margin in subjects with a positive result on LightPath® Imaging.
- Negative predictive value - The probability of clear margin in subjects with a negative result on LightPath® Imaging.
- Positive likelihood ratio (LR+) = sensitivity/1-specificity
- Negative likelihood ratio (LR-) = 1-sensitivity/specificity
- Diagnostic odds ratio (DOR) = (TP/FP)/(FN/TN)

As a sensitivity analysis, the primary analysis will be repeated using the ITT analysis set and for the combined per protocol set.

Analysis will be performed on the approximately 360 margins (60 patients x6 margins). The number of false positive, false negative, true positive, and true negative margins identified by intraoperative CLI + FAR LightPath® imaging will be reported.

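### Protocol 11.7.1 interchanges the FP and FN labels in the confusion matrix, against its own correct formulas, so the reported error counts could be reversed; the likelihood-ratio formulas also lack brackets

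*Protocol*

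**What the plan says.** Protocol section 11.7.1 sets out the primary analysis as a two-by-two table. Its column heading is "standard-of-care histopathology", split into positive and negative; its rows are CLI + FAR LightPath imaging, positive and negative. The rows read "Positive | a (TP) | b (FN) | a+b" and "Negative | c (FP) | d (TN) | c+d", and the key beneath is "TP = true positive; FP = false positive; FN = false negative; TN = true negative".

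Below the table, sensitivity is a/(a+c), specificity is d/(b+d) and overall agreement is (a+d)/(a+b+c+d). Sensitivity is also defined in words as "The proportion of subjects with positive margin confirmed by histopathology who have a positive result on LightPath® Imaging", and specificity as "The proportion of subjects with clear margin confirmed by histopathology who have negative result on LightPath® Imaging". PPV and NPV are defined in words only. The diagnostic odds ratio (DOR) is written with the labels, as (TP/FP)/(FN/TN). The positive likelihood ratio is printed as "Positive likelihood ratio (LR+) = sensitivity/1-specificity"; the negative one is printed in the same unbracketed style.

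The section ends with an analysis of about 360 margins and this commitment: "The number of false positive, false negative, true positive, and true negative margins identified by intraoperative CLI + FAR LightPath® imaging will be reported". Section 11.7.2 then says that the cavity-shaving comparison with histology and the WLE comparison with specimen x-ray will be assessed in the same way as in 11.7.1.

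**The concern.** Under the table's own key, an imaging-positive result with negative histology is a false positive, and an imaging-negative result with positive histology is a false negative. The table prints these two labels the other way round.

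The FP and FN counts are a named output, and the table is the only place where the protocol ties the terms FP and FN to particular cells. No letter formula protects those counts. An analyst who fills in the table as printed and copies out the cells by label would report the two error types reversed.

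The two errors mean different things to a reader of the results. A false positive can lead to an extra cavity shaving. A false negative is a positive margin that imaging missed. Reversal would make a device that over-calls look like one that misses disease, or the other way round. The same risk carries to the secondary comparisons that point back to 11.7.1.

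The unbracketed likelihood ratios are a second, smaller notation fault in the same list.

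**Working it through.** **Step 1: which label belongs to which cell.** The row and column totals (a+b, c+d, a+c, b+d) fix each cell's position.

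| Cell | Imaging | Histology | Printed label | Label under the protocol's key |
|---|---|---|---|---|
| a | positive | positive | TP | TP |
| b | positive | negative | FN | FP |
| c | negative | positive | FP | FN |
| d | negative | negative | TN | TN |

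**Step 2: could the axes be transposed instead?** Suppose rows were histology and columns imaging. The labels on b and c would then be right. But a/(a+c) would divide by all imaging positives, which is PPV, and d/(b+d) would divide by all imaging negatives, which is NPV. Both would contradict the verbal definitions of sensitivity and specificity, and the column heading as well. The section is inconsistent on either reading, and the reading that needs only two labels changed is the printed layout. Letter and label share one cell, so text extraction does not explain the error.

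**Step 3: reproduce the planning values.** Inputs from Protocol 11.6.2: N = 54, positive margins 20%, sensitivity 95%, specificity 90%.

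- a = 54 × 0.20 × 0.95 = 10.26
- c = 54 × 0.20 × 0.05 = 0.54
- b = 54 × 0.80 × 0.10 = 4.32
- d = 54 × 0.80 × 0.90 = 38.88

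The printed letter formulas return 10.26/(10.26 + 0.54) = 95% and 38.88/(4.32 + 38.88) = 90%. They recover the planned values, so they are right for the printed layout.

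**Step 4: expected counts under the printed labels.**

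| | Printed labels | Correct labels |
|---|---|---|
| False negatives | 4.32 (cell b) | 0.54 (cell c) |
| False positives | 0.54 (cell c) | 4.32 (cell b) |

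**Step 5: the one statistic that the protocol writes with labels.** DOR = (TP/FP)/(FN/TN) = (TP × TN)/(FP × FN). Exchanging FP and FN leaves it unchanged: (10.26 × 38.88)/(4.32 × 0.54) = 171 either way.

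**Step 6: likelihood ratios at 95% and 90%.**

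- LR+ as printed: 0.95/1 - 0.90 = 0.05. With brackets: 0.95/(1 - 0.90) = 9.5.
- LR- as printed: 1 - 0.95/0.90 = -0.056. With brackets: (1 - 0.95)/0.90 = 0.056.

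**The case against.** The strongest reply is that no primary estimate is wrong as specified. Sensitivity, specificity and overall accuracy, the named primary measures, each have a correct letter formula and a correct verbal definition, and PPV and NPV are correctly defined in words. The DOR is immune to the swap. This stands in full.

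A reader might still infer that sensitivity and specificity would come out as PPV and NPV. With the printed labels, TP/(TP+FN) becomes a/(a+b) = 10.26/14.58 = 70.4%, and TN/(TN+FP) becomes d/(c+d) = 38.88/39.42 = 98.6%. The algebra is right, but the protocol prints neither formula. To get there, an analyst would have to set aside the printed formulas and definitions, bring in others and pair them with the faulty labels. The document does not support this as a consequence of the plan.

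It is also fair to say that reversal of the counts is a risk and not a certainty. The commitment to report them uses the ordinary terms, and an analyst who goes by their ordinary meaning will count correctly. Further, that commitment concerns about 360 margins, whereas the counts in the working are per patient. The protocol gives no margin-level rate of positivity, so the margin-level reversal cannot be sized from it.

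On the likelihood ratios, these are named standard statistics, and a negative ratio would be noticed at once. The missing brackets are unlikely to reach a report. The formulas are nevertheless wrong as printed.

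Finally, the labels play no part in intraoperative decisions, which rest on the images and the surgeon's discretion (8.6.2, 8.6.4). They bear only on how errors are tabulated afterwards.

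What survives is that the table contradicts its own key, formulas and definitions, and that a planned output depends on the part that is wrong.

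**Conclusion.** The FP and FN labels in the 11.7.1 table are interchanged. This follows from the printed layout and the protocol's own key, and needs no assumption about data.

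The consequence is limited. If the labels are followed, the reported FP and FN counts are reversed, in the margin-level analysis and in any secondary analysis that takes over the template. The illustration of 4.3 against 0.5 holds per patient and rests on the 11.6.2 planning values; other values would change the two numbers but not the reversal. Sensitivity, specificity, overall accuracy, PPV, NPV and the DOR, as the protocol defines them, are not compromised, and the finding should not be read as casting doubt on the primary result.

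The likelihood-ratio formulas are incorrect as written and need brackets. This is typographic and secondary.

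Overall this is a genuine inconsistency of modest severity, worth correcting before the analysis is programmed.

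**What to change.** In the 11.7.1 table, relabel cell b as FP and cell c as FN. Leave the letter formulas, the verbal definitions and the DOR as they are.

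Write LR+ = sensitivity/(1 - specificity) and LR- = (1 - sensitivity)/specificity.

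The corrected table then also serves the analyses in 11.7.2 that refer back to it. The cost is two labels and two pairs of brackets, with no effect on design, sample size, data collection or conduct.

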| Purpose             | 
This study is a prospective, single arm interventional study to evaluate the diagnostic accuracy of intraoperative Cerenkov luminescence imaging (CLI) plus flexible autoradiography (FAR) using the LightPath® Imaging System for intraoperative tumour margin assessment compared to post-operative standard-of-care histopathology in women undergoing breast-conserving surgery for breast cancer.
 
The intraoperative LightPath® images will be used to inform the operating surgeon about potentially detectable cancer at the margins of the excised specimen in an attempt to achieve better guided cancer surgery and complete tumour excision with clear resection margins. If a positive excision margin is detected on intraoperative LightPath® images, the operating surgeon will take a cavity shaving of the corresponding margin, provided more tissue can be taken.
 
Subsequent LightPath® imaging of the cavity shaving will inform the operating surgeon on the margin status of the shaving. If a positive excision margin is detected on intraoperative LightPath® images, the operating surgeon will take a further cavity shave of the corresponding margin, provided more tissue can be taken.
 
The resection margin status of the WLE specimen and cavity shavings (if any), as assessed by LightPath® CLI + FAR imaging will be compared with final histopathology results. A positive margin on histology will be defined as
 
 
• Invasive carcinoma: positive: <math>< 1\text{mm}</math>; negative <math>\geq 1\text{mm}</math>
 
• Ductal carcinoma in situ (DCIS) (if present): positive: <math>< 2\text{mm}</math>; negative <math>\geq 2\text{mm}</math>.
 
 |

|                                            |                                                                                                                                                                                                                                                                                                                                                                                                                                                                                                                                              |

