### 8.6.2. BCS only

Participants scheduled to have BCS will be administered  $^{18}\text{F}$ -FDG intravenously in the Nuclear Medicine Department, approximately 145 minutes prior to CLI + FAR LightPath® imaging. BCS will be performed as per standard of care. Following resection, the WLE specimen and shavings (if any) will be examined intraoperatively using CLI + FAR LightPath® imaging. If the surgeons detect a positive signal, they will perform cavity shavings of the resection cavity area corresponding to the positive signal area. It will be at the surgeon's discretion to choose whether to act based upon the intraoperative LightPath® images.

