#### **8.6.8. Histopathological assessment**

The WLE specimens and cavity shavings will then be examined according to the standard of care histopathology analysis as per the routine pathway at Synlab, Histopathology laboratories, St. Thomas' Hospital. Details of tumour dimensions along with all other histopathology minimum dataset items will be recorded. The distance from the tumour to the radial margins (medial, lateral, superior, inferior, posterior and anterior) will be recorded.

For the histopathology central assessment of the WLE, margins are defined (Toss et al 2017) as either:

- Invasive carcinoma – positive <1mm; negative ≥1mm
- DCIS - positive: <2mm; negative ≥2mm

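### Section 11.7.1 allows a patient flagged only at a clear margin to score as a true positive, because the primary sensitivity and overall accuracy require no match of site

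*Protocol*

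**What the plan says.** Protocol section 11.7.1 names sensitivity, specificity and overall accuracy as the primary measures and words each per subject. Sensitivity is "The proportion of subjects with positive margin confirmed by histopathology who have a positive result on LightPath® Imaging". Specificity is "The proportion of subjects with clear margin confirmed by histopathology who have negative result on LightPath® Imaging". Overall accuracy counts subjects whose margin status is correctly classified. None of these refers to which margin is positive, and no rule is given for reducing six margins to one result per patient.

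The same section then turns to margins: "Analysis will be performed on the approximately 360 margins (60 patients x6 margins"), and "The number of false positive, false negative, true positive, and true negative margins identified by intraoperative CLI + FAR LightPath® imaging will be reported". It does not say how the margin counts relate to the subject-level statistics.

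Elsewhere the protocol is specific about site. In the Synopsis, after a positive image, "the operating surgeon will take a cavity shaving of the corresponding margin, provided more tissue can be taken". In section 8.6.2, if the surgeons see a signal, "they will perform cavity shavings of the resection cavity area corresponding to the positive signal area". Section 8.6.8 provides the matching histology: "The distance from the tumour to the radial margins (medial, lateral, superior, inferior, posterior and anterior) will be recorded". Section 8.6.3 has sutures and clips marking the orientation of the specimen, with extra sutures possible to map image to histology.

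**The concern.** The image is used to decide where to cut. Take a patient whose medial face lights up and is clear on histology, while the lateral face has invasive tumour at less than 1 mm. Healthy medial tissue is shaved and the lateral disease is not flagged. Under the subject-level wording this patient has a positive margin and a positive LightPath result, so she can enter the primary sensitivity and overall accuracy as a success.

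Signal at a clear margin is plausible. Section 5.3 says the scintillating film produces light when tumour is within about 3 mm of the surface, whereas section 8.6.8 calls a margin positive only below 1 mm for invasive carcinoma or below 2 mm for DCIS. Tumour between those limits could light up a margin that histology calls clear.

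At stake is the meaning of the main result. Section 11.7 judges the device on the primary endpoint analysis, and section 11.6.2 sizes the study in patients. A reader will take the reported sensitivity as how often the device points to the involved margin. Section 11.7.2 borrows its method from 11.7.1, so the cavity-shaving and specimen x-ray comparisons inherit the wording.

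**Working it through.** **Inputs from the protocol.** Planned sensitivity 95%, specificity 90%, prevalence of positive margins 20%, 54 patients analysed (section 11.6.2, taken as stated); six margins per patient (sections 8.6.8 and 11.7.1). The plan's margin count reproduces: 60 × 6 = 360. With 54 analysed patients it would be 54 × 6 = 324. The protocol gives no figure for disagreement of site, so there is none to reproduce.

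**Assumptions, not in the protocol.** One involved margin per histology-positive patient, margins independent, the same false-positive rate at every clear margin, and a patient called LightPath-positive if any margin is. The 60% sensitivity and the 70% and 50% specificities are illustrative.

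**Step 1, direction.** A histology-positive patient with signal at the involved margin is a true positive under either definition. One with no signal is a false negative under either. Only a patient with signal solely at clear margins changes: true positive as written, false negative if sites must match. The wording can therefore only raise sensitivity. In a histology-negative patient there is no involved margin to match, so specificity is unaffected.

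**Step 2, formula.** Let s be same-margin sensitivity and Sp patient-level specificity. A patient with six clear margins is negative with probability Sp, so one clear margin stays negative with probability Sp^(1/6). A patient missed at her one involved margin has five clear ones and shows a signal somewhere with probability 1 − Sp^(5/6). Excess = (1 − s) × [1 − Sp^(5/6)].

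**Step 3, results.**

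| s | Sp | 1 − Sp^(5/6) | Excess | Reported sensitivity |
|---|---|---|---|---|
| 95% (planned) | 90% (planned) | 0.084 | 0.05 × 0.084 = 0.004 | 95.4% |
| 60% | 90% (planned) | 0.084 | 0.40 × 0.084 = 0.034 | 63.4% |
| 60% | 70% | 0.257 | 0.40 × 0.257 = 0.103 | 70.3% |
| 60% | 50% | 0.439 | 0.40 × 0.439 = 0.176 | 77.6% |

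If the planned 95% is instead read as the reported figure, the same-margin value is 94.5%, a gap of about 0.5 points. Overall accuracy rises by prevalence times the excess: 0.20 × 0.004 = 0.1 points in the first row and 0.20 × 0.176 = 3.5 points in the last.

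**Step 4, more than one involved margin.** With k involved margins, per-margin sensitivity s and per-margin specificity c, the excess is (1 − s)^k × (1 − c^(6−k)). At s = 60% and patient specificity 90% (c = 0.9^(1/6) = 0.983) it falls from 3.4 points for k = 1 to 1.1 for k = 2 and 0.3 for k = 3.

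**Step 5, one patient.** Expected histology-positive patients: 0.20 × 54 = 10.8, about 11. One wrong-site patient moves sensitivity by 1/11 = 9 points.

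**The case against.** The strongest reply has four parts.

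- **No stated rule.** A reader might infer that the protocol adopts a positive-anywhere rule and that the reported sensitivity is therefore inflated. The text does not go that far: it gives no collapsing rule, and a SAP could add a matching requirement. This stands against any claim that inflation is certain. It does not remove the point, because the protocol itself fixes the definitions, and read literally they ask only for a positive result.
- **Site is already measured.** A reader might also infer that the trial never measures detection at the right place. That is wrong. Section 11.7.1 promises true and false positive and negative counts per margin, and in the example above the medial face would be a false positive and the lateral face a false negative. But these counts are not linked to the subject-level statistics, so they show the problem without correcting those figures.
- **Noise is penalised elsewhere.** It is tempting to say that a noisier device simply looks better. Specificity and overall accuracy are also primary, and about 80% of patients are expected to be histology-negative. A device noisy enough to rescue 26% or 44% of missed patients would show 70% or 50% specificity against a planned 90%. This stands, although the sensitivity figure remains wrong.
- **The effect is small.** At the planned values it is 0.4 points, about 0.05 of a patient among 11, and the exact 95% interval for 10 of 11 is 58.7% to 99.8%. This also stands for the planned case. The larger figures need a device well below its design assumptions, but the trial is run to find out whether those assumptions hold.

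**Conclusion.** The point holds as a fault in the definition. Section 11.7.1 allows a wrong-site signal to count as detection in the primary sensitivity and overall accuracy, although the intervention acts at the flagged site and histology is recorded by site.

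The error runs one way for sensitivity. Its expected size is negligible if the device performs as planned and reaches about 18 points in the least favourable case examined. These sizes rest on the independence, equal-rate and single-margin assumptions, and they shrink when several margins are involved. In a sample with about 11 histology-positive patients, a single case is visible in the result. The documents do not show that sensitivity will be materially overstated. They show that the wording permits it and that the data to prevent it are already planned.

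**What to change.** In section 11.7.1:

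1. Define a patient-level true positive as a histology-positive patient with LightPath positive at one or more histology-positive margins, matched on the six recorded orientations.
2. Count a histology-positive patient with signal only at clear margins as a false negative for sensitivity and as misclassified for overall accuracy. Report the number of such patients.
3. Leave patient-level specificity unchanged.
4. Take PPV, NPV, likelihood ratios and the diagnostic odds ratio from the site-matched margin-level table, with intervals that allow for clustering within patient. Exact binomial intervals would treat a patient's six margins as independent. The separation is needed because a wrong-site patient is a miss for sensitivity yet does carry a positive signal. Forcing both facts into one patient-level two-by-two table would make its statistics inconsistent.

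While editing, correct the table's off-diagonal labels. The LightPath-positive, histology-negative cell is marked FN and its counterpart FP, although the sensitivity and specificity formulas are right for the layout.

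The cost is protocol wording, a variable derived from data already planned, and a little more analysis for the clustered intervals. Reported sensitivity may be slightly less favourable. No clinical procedure changes.

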### 11.6.2. Sample Size Determination

The primary endpoint of the study is to report the sensitivity and specificity of CLI + FAR LightPath® imaging for tumour detection compared to positive tumour detection using standard-of-care histopathology methodology (positive margin of a WLE sample).

Using an estimate of the incidence of positive excision margins on histopathology as 20%, with 95%-confidence ( $\alpha = 0.05$  two-sided) and with 10% precision, a sample size of 54 patients will provide sufficient power to detect sensitivity of 95% and specificity of 90% (Cameron and Baldock 1998). To allow for any potential drop-out or non-analysable subjects a total sample size of 60 patients will be enrolled to attain  $N = 54$  patients in the analysis.

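### Protocol 11.7.1 prints both likelihood ratio formulas without brackets and asks for ratios to be shown as percentages with exact intervals; a minor correction to supplementary statistics

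*Protocol*

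**What the plan says.** Section 11.7.1 lists eight accuracy statistics to be presented "as a percentage together with 95% exact confidence intervals". Five are proportions: sensitivity, specificity, overall accuracy, and the positive and negative predictive values. The other three are ratios. Two of them are defined as "Positive likelihood ratio (LR+) = sensitivity/1-specificity" and "Negative likelihood ratio (LR-) = 1-sensitivity/specificity". The third, the DOR, is the quotient of TP/FP and FN/TN, and both inner fractions are bracketed. The same section names sensitivity, specificity and overall accuracy as the primary outcome measures.

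Section 11.7.2 assesses two secondary outcomes in the same way as the primary one: agreement with histopathology for cavity shavings, and agreement with specimen x-ray for the wide local excision specimens.

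The planning values are in section 11.6.2, which states that "a sample size of 54 patients will provide sufficient power to detect sensitivity of 95% and specificity of 90" (per cent). It takes the incidence of positive margins on histopathology as 20%.

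**The concern.** There are two stated faults.

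- **Formulas.** Division comes before subtraction. LR+ as printed is therefore sensitivity minus specificity, and LR- as printed is one minus the quotient of sensitivity and specificity. A likelihood ratio cannot be negative, yet the printed LR- is negative whenever observed sensitivity exceeds observed specificity. Loss of brackets in text conversion is an unlikely explanation, because the other formulas in the section keep theirs.
- **Presentation rule.** LR+, LR- and DOR have no upper bound, so a percentage is the wrong scale. For the likelihood ratios, the exact binomial interval that fits the five proportions does not apply.

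A program or table shell written from this section would inherit both faults, and section 11.7.2 would repeat them in two further analyses. At stake is the correct reporting of supplementary statistics. The primary result is not at risk.

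**Working it through.** **Inputs.** Sensitivity 0.95, specificity 0.90, prevalence 0.20 and N = 54, all from section 11.6.2. The protocol states no numerical LR or DOR, so there is no figure of its own to reproduce here. N = 54 serves only as an input, and it agrees with 60 enrolled less 10% drop-out: 60 × 0.90 = 54.

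**Step 1: the formulas at the planning values.**

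| Statistic | As printed | As intended |
|---|---|---|
| LR+ | 0.95/1 − 0.90 = 0.05 | 0.95/(1 − 0.90) = 9.5 |
| LR- | 1 − 0.95/0.90 = −0.056 | (1 − 0.95)/0.90 = 0.056 |

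In 400,000 simulated trials at these values with N = 54, the printed LR- is negative in about 75%. It is not negative in every trial.

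**Step 2: the DOR.** (TP/FP)/(FN/TN) = TP × TN/(FP × FN), which is the standard form. At the planning values it is (0.95 × 0.90)/(0.05 × 0.10) = 171. The formula is right; only the percentage scale is wrong. The table in section 11.7.1 has the FN and FP labels interchanged, but this does not change the DOR because the two counts enter as a product. Below, FN means positive on histology and negative on imaging.

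**Step 3: how often FN is zero (supporting a caution only).** Each patient is a false negative with probability 0.20 × 0.05 = 0.01.

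- N = 54: (1 − 0.01)^54 = 0.581.
- N = 60: (1 − 0.01)^60 = 0.547.
- Exactly 11 histology-positive patients (54 × 0.20 = 10.8): 0.95^11 = 0.569.

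Section 11.7.1 also plans an analysis of about 360 margins, for which no prevalence is given. Assuming independent margins and a margin-level prevalence between 3.3% (0.20/6) and 20%, with 324 (54 × 6) to 360 margins, the probability of FN = 0 runs from (1 − 0.033 × 0.05)^324 = 0.58 down to (1 − 0.20 × 0.05)^360 = 0.03.

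**Step 4: what can be reported when FN = 0.** Take 11 of 11 positives detected and 39 of 43 negatives cleared.

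- LR- = 0, with a score-based 95% upper limit of about 0.29.
- DOR is infinite, with an exact conditional 95% interval from 15.4 to infinity.
- Sensitivity is 11/11, with an exact lower limit of 0.025^(1/11) = 71.5%.
- Negative predictive value is 39/39, with an exact lower limit of 0.025^(1/39) = 91.0%.

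An empty cell therefore still allows a useful statement, provided that the interval limit is shown.

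**The case against.** The strongest reply is that this is typography. Both likelihood ratios are named in full and have one standard definition, so a competent analyst would not report a negative one. They are also supplementary: they carry no threshold, decision rule or sample-size role, and section 11.7 describes most of the analysis as descriptive. The negative predictive value, in the same list and with a valid exact interval, already tells the reader how far a clear image can be trusted. All of this stands, and it sets the weight at minor. It does not make the printed formulas or the percentage rule correct.

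A reader might go further and infer that the DOR rule is faulty because FN = 0 is likely. The documents do not support that:

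- The DOR formula is algebraically correct.
- Handling of empty cells is commonly left to the statistical analysis plan, which is not at hand.
- The protocol asks for exact intervals without naming a binomial or log-scale method. An exact conditional interval for an odds ratio exists and tolerates an empty cell.
- The 58% holds per patient. At margin level it depends on a prevalence that the protocol does not give.

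A reader might also infer that a bare LR- of 0 would pass as a perfect rule-out. The exact intervals for sensitivity and negative predictive value, required in the same list, would show otherwise.

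**Conclusion.** The concern holds as a minor correction. Two formulas are stated wrongly: at sensitivity 0.95 and specificity 0.90 they return 0.05 for 9.5 and −0.056 for 0.056. The presentation rule does not fit three of the eight listed statistics, and both faults pass into two secondary analyses. Sensitivity, specificity and overall accuracy are untouched.

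The sparse false-negative cell is a caution and no more. The figure of about 58% assumes one result per patient, N = 54, 20% prevalence and 95% sensitivity.

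**What to change.** In section 11.7.1:

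1. Write LR+ = sensitivity/(1 − specificity) and LR- = (1 − sensitivity)/specificity.
2. Limit the percentage with exact 95% confidence interval to sensitivity, specificity, overall accuracy, and the positive and negative predictive values.
3. Report LR+ and LR- as ratios with an interval that remains valid with a zero cell, for example a score-based one. Report DOR as a ratio with an exact conditional interval.
4. When LR- is 0 or DOR is infinite, show the finite interval limit beside it. This could equally go in the statistical analysis plan.

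Section 11.7.2 needs no separate edit, since it refers back to 11.7.1. The cost is a few lines of wording, with no new data, participants or procedures. The DOR interval may be open at the upper end, which is a fair picture of about 11 positive patients. Adding 0.5 to every cell would avoid the infinity, but at the planning values it lowers the median DOR to about 118 against a true 171, so the exact conditional interval is preferable.
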